### Secondary outcomes

Piper Fatigue Scale—to assess the levels of exhaustion and fatigue [28].Neuropathy Questionnaire (EORTCOLO QLQ-CIPN20) [27].

### Participant timeline {13}

The schedule of enrolment, interventions, and assessments are shown in Fig. 2.

**Fig. 2 Fig2:**
[figure not shown]
Content for the schedule of enrolment, interventions, and assessments

### Sample size {14}

One hundred and fifty cancer patients aged 18–65 years (stage III colon cancer patients and breast cancer patients with lymph node involvement) will be recruited via advertisements in Hadassah Medical Center and Tal Aviv University. The sample size is based on data from the WHO Disability Assessment Schedule (WHODAS 2.0), which has been used internationally to assess function and disability among a healthy population versus an unhealthy population [26]. The expected difference in the questionnaire scores between the two groups is 15 points and the average standard deviation is 15.08. The sample calculation includes a type 1 error of alpha equal to 0.05 with a power of 80%. According to this calculation, 16 participants are needed in each of the three study groups. Because we anticipate the withdrawal of some of the participants and because of the clinical condition of all participants, a number of 50 participants per group was selected.

### Recruitment {15}

Participants in this study will be recruited via flyers on social media (Facebook and Instagram), from references from colleagues (university faculty members, clinicians, and researchers), and via flyers/posters on Hadassah Medical Center.

### Assignment of interventions: allocation

#### Sequence generation {16a}

Simple randomization will be used in this study. Participants who met the inclusion criteria will be randomized to one of three groups, using specific online software (https://www.randomizer.org/). Ratio allocation will be 1:1:1 (approximately).

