**Methods:**

This randomized controlled trial will include 150 cancer patients aged 18–65 years with stage III colon cancer or breast cancer patients with lymph node involvement. Participants in the aquatic exercise intervention group will undergo an 8-week, twice-weekly group-based Ai-Chi program, while the on-land exercise group will perform identical exercise. The control group will not engage in any exercise.

The primary outcome will be assessed using an employment barriers questionnaire, capturing return to work date and working hours and daily life participation and activity and quality of life. Secondary outcomes include exhaustion, fatigue, and neuropathy. Data will be collected at baseline, post-intervention (8 weeks), and at 3,12, and 24 months. Mixed variance analyses will explore relationships among groups and over time for independent variables, with separate analyses for each dependent variable.

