### Eligibility criteria {10}

Criteria for inclusion in the study will be: (a) age between 18–65; (b) diagnosis of cancer; and (c) a score above 26 on the cognitive MOCA test [24]. Volunteers with orthopedic injuries that in the opinion of the attending physician prevent their participation in physical exercise, or individuals engaged in other physical activity on a regular basis, will not be eligible to participate in the present study. Recruitment of colorectal cancer patients and breast cancer patients for the study will be within 3 months of cessation of chemotherapy treatment.

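### Two cancers are enrolled, but neither the simple randomisation nor the stated group-by-time analysis takes account of cancer type: a minor, cheaply avoided loss of balance and precision

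*Protocol article*

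**What the plan says.** Sequence generation {16a} of the protocol article commits to an unrestricted scheme: "Simple randomization will be used in this study". It adds "Ratio allocation will be 1:1:1 (approximately", so some inequality between arms is accepted from the outset. Sample size {14} finds 16 per group sufficient and then, to allow for withdrawals and the patients' condition, says that "a number of 50 participants per group was selected".

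Two cancers are enrolled. Eligibility criteria {10} speaks of "Recruitment of colorectal cancer patients and breast cancer patients for the study", and Sample size {14} of "stage III colon cancer patients and breast cancer patients with lymph node involvement". The expected proportion of each is not stated. No section mentions blocks, strata or minimisation.

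Statistical methods {20a} describes mixed analyses of variance, one per outcome, with group and time as the independent variables. Cancer type does not appear. Implementation {16c} gives the allocation to a team member outside recruitment, assessment and delivery. Blinding {17a} makes the trial open to participants and caregivers.

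**The concern.** Cancer type is recorded before randomisation, so balancing it needs no extra data. All patients enter within three months of finishing chemotherapy, and the outcomes include fatigue, neuropathy and return to work. It is plausible that the two cancers differ on these, although the article gives no data to show it. With three arms of about 50 and no stratification, the case mix can differ between arms by chance, and the analysis as stated would not correct for it. What is at stake is some precision, and the ease of reading the water-versus-land result: the two programmes use the same movements, so any true difference may be modest and a visible difference in case mix would invite doubt.

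**Working it through.** **The plan's own figure.** Inputs from Sample size {14}: "The expected difference in the questionnaire scores between the two groups is 15 points" and "the average standard deviation is 15.08", alpha 0.05 (taken as two-sided), power 80%.

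n per arm = 2 × (1.960 + 0.842)² × (15.08/15)² = 2 × 7.849 × 1.0107 = 15.9, so 16. The stated figure is reproduced.

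**Arm sizes under simple randomisation of 150 patients.**
- SD of one arm = √(150 × 1/3 × 2/3) = 5.8, with a 95% range of 39 to 61.
- The exact multinomial gives 50/50/50 in 0.55% of trials. The smallest arm averages 44. It is 40 or fewer in 14% of trials and 30 or fewer in 0.07%.
- Power at the plan's own difference is 99.9% for 50 v 50 and 99.8% for 40 v 60.
- A smaller difference with 80% power at 50 v 50 is 2.802 × 15.08 × √(2/50) = 8.4 points. At 40 v 60 the variance rises by (1/40 + 1/60)/(2/50) = 1.04, and power becomes 78.4%.

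Unequal arm sizes therefore cost very little.

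**Cancer mix under simple randomisation.** The breast share is an assumption, shown over 50% to 90%. Each row is 200,000 simulated trials of 150 patients.

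| Assumed breast share | Largest of three gaps ≥10 points | Largest of three gaps ≥20 points | Water v land ≥10 points | Water v land ≥20 points |
|---|---|---|---|---|
| 50% | 59% | 12% | 32% | 4.7% |
| 70% | 53% | 8% | 28% | 3.1% |
| 80% | 43% | 3% | 22% | 1.3% |
| 90% | 23% | 0.2% | 10% | 0.07% |

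Hand check of the last column: the SE of the gap between two arms of about 50 is √(p(1−p) × 2/50). This is 10.0, 9.2, 8.0 and 6.0 points for the four rows, so 20 points is 2.0, 2.2, 2.5 and 3.3 SEs. The two-sided normal tails are 4.6%, 2.9%, 1.2% and 0.09%, in line with the simulation.

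**What an imbalance could do.** Assume, for illustration only, that the two cancers differ by 0.5 within-cancer SD on an outcome.
- A 20-point gap shifts an unadjusted comparison by 0.20 × 0.5 = 0.10 SD. The SE at 50 v 50 is √(2/50) = 0.20 SD, so the shift is half a standard error.
- Averaged over randomisations, leaving cancer type out inflates the variance by 1 + p(1−p) × 0.5². This is 1.06 at 50% breast, 1.05 at 70% and 1.02 at 90%.

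**Effect of the remedy.** Permuted blocks within the two cancers, 70% breast assumed, 20,000 runs per block size:

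| Block size | Largest minus smallest arm: mean (maximum) | Largest gap in breast share | Exactly 50/50/50 |
|---|---|---|---|
| 3 | 0.9 (2) | 2 points | 56% |
| 6 | 1.3 (4) | 4 points | 39% |
| 9 | 1.7 (6) | 6 points | 23% |

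Under simple randomisation the mean difference between the largest and smallest arm is 12. Stratification is what fixes the mix. Forcing arms of exactly 50 without strata still leaves a largest gap of at least 20 points in 8.5% of trials at 70% breast, against 8% with simple randomisation.

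**The case against.** A reader might infer that simple randomisation breaks the plan for 50 per arm. It does not. The article says the ratio is approximate, the 50 carries a wide margin over the 16 required, and the power loss is trivial. Stratified blocks also miss exact equality in 44% to 77% of runs at the block sizes checked. Nor do exercise classes of five add much: final arm size leaves at most one part-filled class per exercise arm. All of this stands.

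A reader might also infer bias. Chance imbalance under a valid randomisation is not bias, and the standard error of the unadjusted comparison already allows for it. That stands too.

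The imbalance figures depend on an unstated case mix and are small if one cancer dominates. The maximum over three arms also overstates what happens to any single comparison. Both remarks are fair, which is why the range and the water-versus-land columns are shown.

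No passage shows that cancer type predicts the outcomes. For the questionnaires, the baseline measurement and the group-by-time term absorb a stable difference between cancers. That holds in part. It does not help the date of return to work, which has no baseline value, or a difference between cancers in the course of recovery.

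Finally, covariates are often left to a statistical analysis plan, which is not shown and may already include cancer type. If it does, that half of the remedy is done. The allocation method, however, is fixed in the article itself.

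**Conclusion.** The point holds as a minor one about efficiency and credibility. The article fixes an allocation without strata and states an analysis by group and time only, so a baseline factor known at entry is left to chance. A gap of 20 points in breast share somewhere among the three arms has a probability of about 12% at a 50% breast share, falling to 0.2% at 90%. For water versus land it is about 5%, falling to 0.1%. If the cancers differed by 0.5 SD, such a gap would move a comparison by half a standard error, and omitting cancer type would cost 2% to 6% in variance. These sizes rest on an assumed case mix and an assumed prognostic difference, neither of which the article gives. The documents do not support calling the randomisation invalid, the arm sizes contradictory or the trial underpowered on this ground.

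**What to change.** 1. Add cancer type (breast versus colorectal) as a covariate in the model for each outcome, and write this down before any comparison by arm. It costs nothing, needs no new data, covers patients already randomised and recovers much of the precision. If an analysis plan already provides for it, no change is needed here.
2. For patients still to be randomised, replace simple randomisation with 1:1:1 permuted blocks of randomly varying size, stratified by cancer type. The independent allocator described under Implementation {16c} should hold the list, and the block sizes should not be disclosed to recruiters. Recruitment began in April 2023 and is planned to run to August 2027, so this can still reach later patients, but it cannot undo imbalance already present.

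The second step needs a new allocation list and a protocol amendment approved by both ethics committees before use. It also gives up some unpredictability in an open trial, limited by the varying block sizes and by the allocator's separation from recruitment. If the sponsor judges that too much, the first step alone is a reasonable minimum.

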### Concealment mechanism {16b}

Intervention group assignment to participants or therapists cannot be concealed due to the nature of interventions. The allocation will be made by a member of the research team who will not be involved in the screening or group intervention.

### Implementation {16c}

A member of the research team who will not be involved in patient recruitment, assessment, or delivering the intervention will perform randomization and allocation.

### Assignment of interventions: Blinding

#### Who will be blinded {17a}

Due to the nature of this intervention, treatment allocation cannot be blinded to the participants or to the caregivers. Participants receive an explanation about the type of intervention, and caregivers are aware that everyone is a patient and know what type of treatment they provide.

### Procedure for unblinding if needed {17b}

This trial is not blinded to the participants or caregivers.

### Data collection and management

#### Plans for assessment and collection of outcomes {18a}

Most of the outcomes are collected in the hospital by questionnaires. In cases where participants do not come to a follow-up visit, data will be collected by phone interview.

#### Plans to promote participant retention and complete follow-up {18b}

Upon completion of the intervention, participants will be contacted by e-mail and phone calls to encourage them to complete the follow-up.

### Data management {19}

All data obtained will be at a secured platform. Patients will accept the informed consent and will be contacted by a researcher data collection meeting. The members of the research team in charge of the data collection will be trained. Data will be stored in a secure office at the Hadassah Medical Center. After that, patients’ data will be anonymized by a unique ID code on the dataset and will be stored in a secure server and the computer will have a password to be accessed only by the principal investigators from Tel Aviv University.

### Confidentiality {27}

Before entering the study, participants will complete the initial screening and the informed consent. Participants’ information will be encoded with a unique ID number to maintain confidentiality. The database will be protected on a computer with password security on a secured platform. Only the principal investigator from Tel Aviv University will have access to the data.

### Plans for collection, laboratory evaluation and storage of biological specimens for genetic or molecular analysis in this trial/future use {33}

No biological samples will be collected.

### Statistical methods

#### Statistical methods for primary and secondary outcomes {20a}

Every participant will be assigned a random study identifier number, ensuring the privacy of their personal data. The statistical analyses will be conducted in a way that prevents the identification of individual patients. We will conduct a series of mixed variance analyses to identify relationships and associations between groups, as well as changes over time within each group (independent variables). The dependent variables will be primary and secondary outcomes, and a separate analysis will be performed for each variable.

Additionally, we will conduct various analyses to explore the relationships between changes in the dependent variables.

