### Objectives {7}

Based on the literature review described above, the objectives of the present study are:

(A) To examine the effects of an 8-week physical activity program in water, on time to return to work, work hours, perception of work-related difficulties, and work absenteeism, among cancer patients, as compared to an intervention group undergoing identical physical exercise on land, and a third group with no additional exercise.(B) To examine the effects of an 8-week physical activity program in water on activity and participation in the daily life and quality of life of cancer patients compared with the other two intervention groups (the same physical activity on land and the group without further physical exercise).(C) To examine the effects of an eight-week water exercise program on exhaustion, fatigue, and neuropathy in cancer patients compared with the other two intervention groups (the same physical exercise on land and the group without further physical exercise).

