### Primary outcome

Employment Barriers Questionnaire [25] and Date of return to work and duration of working hours—self-report by the study participants.WHODAS 2.0—to examine the degree of activity and participation in daily life [26].EORTC QLQ-C30—to evaluate the quality of life from the point of view of the participant [27].

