### Methods in analysis to handle protocol non-adherence and any statistical methods to handle missing data {20c}

To address protocol non-adherence, intervention physiotherapists will receive intervention protocol. Missing data will be imputed using the random forest method.

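### Date of return to work, part of the primary outcome, is assigned a group-by-time variance analysis that does not fit a single, censorable event time, and no rule covers patients who have not returned

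*Protocol article*

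**What the plan says.** Objective A in the Protocol article (Objectives {7}) concerns the effect of the water programme "on time to return to work, work hours, perception of work-related difficulties, and work absenteeism". The Primary outcome section lists, beside the Employment Barriers Questionnaire, WHODAS 2.0 and the EORTC QLQ-C30, "Date of return to work and duration of working hours—self-report by the study participants".

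The statistical methods section {20a} states "We will conduct a series of mixed variance analyses to identify relationships and associations between groups", together with changes over time within each group. It then applies this to everything: "The dependent variables will be primary and secondary outcomes, and a separate analysis will be performed for each variable". Return to work is not excepted, and no time-to-event method is named.

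On incomplete data, section {20c} says "Missing data will be imputed using the random forest method", without qualification. No section says how a patient who has not returned by T4 (24 months after the end of the 8-week programme) is to be coded.

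Eligibility {10} asks for an age range, "b) diagnosis of cancer", a cognitive score and recruitment within a window after chemotherapy. It does not ask for a job before treatment or for being off work at entry.

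**The concern.** A mixed variance analysis compares groups on a quantity measured in the same patient at several time points. A return date is not such a quantity. It occurs at most once, it cannot have a T0 value in someone still off work, and it does not exist for a patient who has not returned by the end of follow-up. That last case is censoring: the patient is known to have been off work at least until last contact. A variance analysis has no place for that information, so some value must be supplied or the patient dropped.

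The one rule the article offers for an empty field is imputation. Random-forest predictions are averages of observed values, so an imputed date cannot fall later than the latest observed return. Used on non-returners, the rule would make the slowest patients look like those who did return, and more so in whichever arm has more of them. Earlier return to work is the benefit on which the article's Discussion builds its socio-economic argument, so the error would fall on a central claim.

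**Working it through.** **The plan's own figure.** The sample size section uses a WHODAS 2.0 difference of 15, SD 15.08, alpha 0.05 (two-sided assumed) and power 80%. n = 2 × [15.08 × (1.960 + 0.842) / 15]² = 15.87, rounded up to 16 per group. The stated 16 reproduces, but it concerns WHODAS 2.0 only and says nothing about return to work.

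**Structure of the outcome against the method.**
- Method {20a}: group and time as factors, one analysis per outcome, assessments at T0 to T4.
- Outcome: one date per patient, no T0 value, no series, absent for non-returners.
- The time factor therefore has nothing to act on. This needs no assumption.

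**Size if non-return is imputed.** From the documents: 50 per arm and follow-up of 8 weeks plus 24 months, about 26 months. Assumed, because the documents give neither: exponential return times, a hazard ratio (HR) of 1.5 or 2, and a control return proportion p of 50% to 95% by 26 months. Two arms were compared.

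Formulas, with C = 26:
- control rate λ = −ln(1 − p)/C; the other arm has rate HR × λ
- restricted mean = (1 − e^(−λC))/λ
- mean date among returners = 1/λ − C × e^(−λC)/(1 − e^(−λC))

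Worked case, p = 50%, HR 2:
- λ = 0.6931/26 = 0.02666 and 0.05332; proportions returning 0.50 and 0.75
- restricted means: 0.50/0.02666 = 18.76 and 0.75/0.05332 = 14.07; true difference 4.69 months
- means among returners: 37.51 − 26 × 0.50/0.50 = 11.51, and 18.76 − 26 × 0.25/0.75 = 10.09
- pooled returner mean: (0.50 × 11.51 + 0.75 × 10.09)/1.25 = 10.66
- after filling blanks from the pooled returners: 0.50 × 11.51 + 0.50 × 10.66 = 11.08, and 0.75 × 10.09 + 0.25 × 10.66 = 10.23; difference about 0.85 months

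A simulation of 2,000 trials per scenario gave 0.82 for that case. In it, a random draw from observed dates stood in for the random forest, and a two-arm mean comparison stood in for the group contrast. Monte Carlo standard error of a power figure is at most √(0.25/2000) = 1.1 percentage points. Results at HR 2:

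| Controls back by 26 months | True restricted-mean difference (months) | Difference after imputation ignoring arm | Share lost | Log-rank power | Power after imputation ignoring arm |
|---|---|---|---|---|---|
| 50% | 4.69 | 0.82 | 83% | 79% | 8% |
| 70% | 5.29 | 1.76 | 67% | 87% | 25% |
| 85% | 4.95 | 2.62 | 47% | 91% | 55% |
| 95% | 3.92 | 2.98 | 24% | 93% | 82% |

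Share lost = 1 − imputed/true; for example 1 − 0.82/4.69 = 83%.

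At HR 1.5, over the same return proportions, log-rank power is 33%, 45%, 49% and 52%, against 5%, 9%, 18% and 35% after imputation ignoring arm.

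If dates are instead imputed once within each arm, the type I error at HR 1 is about 23%, 12%, 9% and 6%. If non-returners are set to 26 months, power at HR 2 is 72%, 84%, 90% and 93%, and the estimate matches the restricted-mean difference.

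**The case against.** The strongest reply is that the article never says non-return counts as missing. A reader might infer that non-returners will be given an invented date; the text does not say so, and coding rules are often left to a full protocol or analysis plan. Setting non-returners to the end of follow-up is equally compatible with the article and would remove nearly all of the loss. This stands, so the imputation consequence is conditional.

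Nor do the documents establish that the effect would be badly diluted. They give no return rate and no hazard ratio, and the loss at HR 2 runs from 83% down to 24% across the assumed range. The inflated type I error needs single imputation within arm, and the article does not say whether imputation is single or multiple. These limits also stand.

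Two further readings are tempting and unsupported. One is that work hours suffer the same fault: hours can be recorded at each visit, and nothing suggests that a patient not working would be blank rather than zero. The other is that absenteeism in objective A has no measure: the Employment Barriers Questionnaire may cover it, and its items are not shown.

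It is also fair that the fault touches one component of a multi-part primary outcome. The questionnaires suit repeated-measures analysis, and the sample size rests on WHODAS 2.0.

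What does not stand is the appeal to an unseen analysis plan for the method itself. The article names the method and applies it to all primary outcomes, so this is a wrong choice that is stated, not a detail left out.

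**Conclusion.** The concern holds for the method. A group-by-time variance analysis is fixed for a date that occurs at most once, has no baseline value and can be right-censored. That follows from the text alone.

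The consequence through imputation is conditional on non-return being treated as missing, which the text permits and does not state. Under that reading the direction is clear: a diluted effect, or with single imputation within arm also too many false positives. The size is not known. It ranges from moderate, if nearly all patients return, to severe, if about half do not. The figures rest on exponential times, two arms of 50, an assumed hazard ratio, and a simple draw in place of a random forest.

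The absence of an employment criterion adds a second gap: patients who had no job, or never stopped work, have no return to time, yet nothing separates their empty field from missing data.

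**What to change.** - In section {20a}, except return to work from the mixed variance analyses. Define it as time from randomisation to first return to work, and analyse it with Kaplan-Meier curves and a log-rank test or Cox model, or with restricted mean time to the end of follow-up.
- Censor patients who have not returned at their last contact.
- In section {20c}, state that non-return is not missing data and is excluded from imputation.
- Define the return-to-work analysis set as patients who had a job and were off work at T0. Both facts precede randomisation, so the restriction keeps the randomised comparison intact. Record employment status at baseline, and ask it retrospectively of patients already enrolled, since recruitment began in April 2023.

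The cost is a change of analysis wording, one baseline item, some retrospective questioning, and an analysis set below 150. The change makes the analysis valid but does not supply power: by 4 × (1.960 + 0.842)²/(ln HR)², a two-arm comparison needs 191 events at HR 1.5 and 66 at HR 2, while two arms hold at most 100 patients. The article should not imply that the WHODAS-based sample size covers this outcome.

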### Trial design {8}

This is the protocol of a parallel-group, controlled, randomized trial, with a pre-post and repeated follow-up measures between-group design.

A three-arm trial is going to be carried out. Participants who meet the recruitment criteria bellow will be randomly assigned to Group 1: Water exercise group, Group 2: Land exercise group, or Group 3: Control group. The assessment will be conducted at five-time points: an initial assessment before being randomized (pretreatment; T0), at the end of the intervention (post-treatment; T1), 3 months after the completion of the intervention (T2), 12 months after the completion of the intervention (T3), and 24 months after the completion of the intervention (T4). CONSORT patient’s flowchart is presented in Fig. 1.

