### Outcomes {12}

Data will be collected by a medical student in the fourth year of studies at the following time points: before the start of the intervention (at baseline), after 8 weeks of intervention, and then at 3, 12, and 24 months from the end of the intervention.

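### Mixed analysis of variance over five unequally spaced visits: if correlation decays with time and no correction is used, group-by-time tests run at about 6% to 10%, and pooled-error contrasts are too liberal late and too conservative early

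*Protocol article*

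**What the plan says.** In the protocol article, the section on statistical methods for primary and secondary outcomes {20a} states: "We will conduct a series of mixed variance analyses to identify relationships and associations between groups". It treats group and change over time as the independent variables and adds that "a separate analysis will be performed for each variable". The abstract repeats the method in similar terms.

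Trial design {8} sets three arms and says: "The assessment will be conducted at five-time points". Outcomes {12} places them at baseline, then "after 8 weeks of intervention, and then at 3, 12, and 24 months from the end of the intervention".

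The article names no covariance structure, sphericity test, degrees-of-freedom correction or error term for follow-up contrasts, and it excludes none of them. Section {20c} imputes missing values by random forest, which fits a complete-data analysis of variance more naturally than a likelihood-based mixed model.

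**The concern.** A group-by-time analysis of variance pools the within-person error over all visits. Its F test for the interaction, and any contrast that borrows the pooled error, is exact only under sphericity. Here that would require the change over 8 weeks to be as variable as the change over about 26 months.

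The outcomes are symptom, function and quality-of-life scores in patients enrolled within 3 months of ending chemotherapy. Scores 8 weeks apart would usually be more alike than scores two years apart. If so, the interaction test is liberal. Pooled-error contrasts then go wrong in both directions: standard errors are too small for the longest follow-up, where a lasting benefit would be claimed, and too large at the end of treatment, where an effect may be easiest to see. The objectives compare water exercise with land exercise and with control, so contrasts between arms will be needed whatever the omnibus test shows.

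**Working it through.** **Plan's own figure.** Sample size {14} gives a difference of 15, SD 15.08, alpha 0.05 and 80% power. With a two-sided test, n = 2 × (1.96 + 0.8416)² × (15.08/15)² = 2 × 7.849 × 1.0107 = 15.9, so 16 per group, as stated. This two-group calculation does not involve sphericity.

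**Inputs from the article.** Three arms, 50 per arm, five visits. With 8 weeks = 8/4.345 = 1.84 months, the visits fall at 0, 1.84, 4.84, 13.84 and 25.84 months.

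**Assumed.** The covariance between visits, because the article gives none; hence a range of structures. Data are normal and complete, so the random forest imputation is not modelled.

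**Closed form for one structure.** Take unit variance and correlation 0.95 per month.
- Correlations of T0 with T1 to T4: 0.910, 0.780, 0.492, 0.266.
- True variance of change from baseline, 2(1 − ρ): 0.180, 0.440, 1.017, 1.469.
- Pooled error (average variance minus average covariance): 0.435. The variance assumed for every change is therefore 2 × 0.435 = 0.870.
- Ratio true/assumed: 0.21, 0.51, 1.17, 1.69.
- Approximate error, 2[1 − Φ(1.96/√ratio)]: T1 about 0.0%, T2 0.6%, T3 7.0%, T4 13.1%.

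**Simulation.** No true effect, 6,000 runs per row, Monte Carlo standard error about 0.3 percentage points. Contrasts are water versus control on change from T0. Entries are rejection rates in %, apart from epsilon.

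| Assumed covariance | Epsilon | Group-by-time, uncorrected | Greenhouse-Geisser | T1 pooled | T2 pooled | T4 pooled | Group main effect |
|---|---|---|---|---|---|---|---|
| Equal correlation 0.5 | 1.00 | 4.9 | 4.8 | 5.0 | 4.7 | 5.2 | 5.2 |
| 0.97 per month | 0.52 | 9.5 | 5.0 | 0.0 | 0.5 | 13.7 | 5.0 |
| 0.95 per month | 0.57 | 8.9 | 5.3 | 0.0 | 0.6 | 13.2 | 4.7 |
| 0.90 per month | 0.67 | 7.9 | 5.3 | 0.0 | 1.5 | 11.2 | 5.6 |
| 0.80 per month | 0.82 | 6.0 | 4.4 | 0.3 | 2.8 | 7.6 | 4.9 |
| Random intercept + decay | 0.67 | 7.7 | 5.1 | 0.0 | 1.3 | 10.9 | 4.6 |
| Random intercept + decay + measurement error | 0.87 | 5.6 | 4.4 | 1.2 | 2.7 | 7.4 | 5.0 |
| Random slope | 0.76 | 6.7 | 4.8 | 1.7 | 1.7 | 12.5 | 5.3 |

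The simulated 13.2% for T4 at 0.95 per month agrees with the closed form (13.1%). Contrasts using their own variance gave 4.5% to 5.4% throughout. A further set of runs at 50 per arm put the T1 contrast as high as 2.5%, hence the range of about 0% to 2.5%.

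T3 was not simulated. In closed form its ratio is 1.14 to 1.20 under pure decay (error 6.7% to 7.3%), so the clear excess is at T4.

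**Gain from baseline adjustment.** With equal variances, adjusting for baseline gives variance (1 − ρ²) against 2(1 − ρ) for change, a reduction of (1 − ρ)/2. At 0.97 per month, T0 to T1 has ρ = 0.945, a reduction of about 3%. At 0.90 per month, T0 to T4 has ρ = 0.066, a reduction of about 47%.

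**The case against.** The strongest answer is that the article does not commit to the faulty version. It does not say that sphericity is assumed, that no correction will be made, or that contrasts will use a pooled error. Such details commonly sit in a statistical analysis plan, which is not shown, and the loose wording could even mean a mixed model. With a Greenhouse-Geisser or Huynh-Feldt correction the interaction test holds at 4.4% to 5.4%. All of this stands. Taken alone, the missing correction would be detail for the analysis plan.

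A reader might also infer more than the documents support:

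- **That the visits cannot meet sphericity.** Unequal spacing alone does not break it. Equal correlation satisfies it at any spacing, and the rate is then 4.9%.
- **That all follow-up contrasts exceed 5%.** Under pooled error the early ones fall well below it.
- **That the group-by-time test is the trial's stated main test.** The article names no such test.
- **That working hours have almost no variance at baseline.** The article gives no figures on this.

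The milder structures matter too: with a stable person effect and measurement error, both plausible for questionnaires, the uncorrected rate is only 5.6%.

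What remains is that the method as named depends on an assumption that the visit schedule makes doubtful. The usual correction does not reach the contrasts that the objectives call for, and a method free of that assumption is available using data already planned.

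**Conclusion.** The point holds in conditional form. If correlation decays over the 26 months and the classical analysis is left uncorrected, the group-by-time test rejects in about 6% to 10% of null trials. Contrasts on the pooled error would reject in about 7% to 14% for T0 to T4 and about 0% to 2.5% for T0 to T1. The group main effect keeps its 5% level.

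These sizes rest on assumed covariances, complete normal data and 50 per arm. They are not a finding that the trial's tests will exceed 5%, because the article leaves open both the correlations and the correction. The reason to act is that a better-suited method can be named now at little cost, and it also makes efficient use of the baseline score.

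**What to change.** In {20a}, for the repeated questionnaire scales, replace the mixed analysis of variance with a mixed model for repeated measures:

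- outcomes at T1 to T4;
- arm by visit;
- the baseline score as covariate, preferably with a visit-specific slope because its correlation with later scores may fall;
- unstructured covariance;
- arm contrasts reported by visit.

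If the analysis of variance is kept, state that the Greenhouse-Geisser correction applies to the within-person tests and that each contrast uses its own error term.

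This changes wording only and needs no new data. Recruitment is expected to run to August 2027, so it can be settled before analysis. The random forest imputation in {20c} should be reconciled with the chosen model, since a likelihood-based model uses the available visits directly. The downside is that intervals for late-visit contrasts may be somewhat wider than with the pooled error; where correlation decays, that width is the honest one.
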